## Abstract

**Background:**

Adolescence is an established period of physical activity decline. Multi-component school-based interventions have the potential to slow the decline in adolescents’ physical activity; however, few interventions have been conducted in schools located in low-income or disadvantaged communities. This study aims to assess the effectiveness of a multi-component school-based intervention in reducing the decline in physical activity among students attending secondary schools located in disadvantaged communities.

**Methods/Design:**

The cluster randomised trial will be conducted with 10 secondary schools located in selected regions of New South Wales, Australia. The schools will be selected from areas that have a level of socio-economic status that is below the state average. Five schools will be allocated to receive an intervention based on the Health Promoting Schools framework, and will be supported by a part-time physical activity consultant placed in intervention schools who will implement a range of intervention adoption strategies. Study measures will be taken at baseline when students are in Year 7 (12–13 years) and again after 12- and 24-months. The primary outcome, minutes of moderate- to-vigorous- intensity physical activity per day and percentage of time in moderate- to vigorous-intensity physical activity (MVPA), will be objectively assessed using accelerometers (Actigraph GT3x+). Group allocation and intervention delivery will commence after baseline data collection. The intervention will continue during school terms through to 24-month follow-up.

**Discussion:**

The study will provide evidence regarding the effectiveness of a multi-component school-based intervention that includes an in-school physical activity consultant targeting the physical activity levels of adolescents in disadvantaged Australian secondary schools.

**Trial registration:**

Australian New Zealand Clinical Trials Registry ACTRN12612000382875.

## Background

Being physically active can prevent numerous chronic diseases including coronary heart disease, obesity, some types of cancers such as colorectal and breast cancers, and improve muscle strength and fitness and aspects of mental health [1,2]. Despite such benefits, population surveys from the United States of America and the United Kingdom have found that only 15.3 percent of 13–18 year olds [3] in the United States of America and as few as 0–7 percent of 11–15 year olds [4] from the United Kingdom being physically active to a sufficient level to improve health. Similarly, the proportion of Australians adolescents aged 13 to 17 years that meet the recommended amount of physical activity is around 15 percent [5].

The transition into adolescence is a recognised period of physical activity decline. Research suggests that moderate to vigorous physical activity drops by up to seven percent per year between the ages of 9 to 15 years, so that by age 15 the majority of adolescents no longer meet the recommended daily amount of activity [6,7]. In addition, the physical activity decline associated with adolescence is steeper among youth from disadvantaged or low income communities [8,9]. Reducing this decline is an important health priority as inactivity tends to track into adulthood [10].

Schools are a key setting for the promotion of physical activity as they have existing curricula, infrastructure, policies and resources to promote physical activity [11] and are also able to reach those from all backgrounds [12]. The effectiveness of multi-component school based physical activity interventions, particularly those that include links to families and communities, has consistently been demonstrated in reviews [13-19]. However, recent reviews of school based physical activity interventions, have identified only three studies focusing on low income groups [13,20-22] each targeting children of primary school age (i.e. aged 6 to 12 years) rather than adolescents.

Schools located in disadvantaged communities face a number of challenges in implementing whole of school physical activity programs, including student, teacher and parent disengagement and high staff turnover [23-26]. In addition, Australian research indicates students from lower socio-economic or disadvantaged backgrounds face barriers in physical activity participation including lack of parental support, cost of school sports, time available for school sport and choice and variety of physical activities offered at school [27,28]. A review of the effectiveness of physical activity interventions in disadvantaged groups, although not specific to schools, concluded that interventions underpinned by a theoretical framework were more likely to be successful, and suggested the importance of focussing on a range of areas including social and professional supports and increasing the length of the intervention period [18]. The Health Promoting Schools (HPS) framework [29] has an emphasis on intervention across a range of areas including school curriculum, school environment and ethos, and partnerships with community and parents. In order to address the challenges of intervening within disadvantaged schools, in addition to the introduction of health strategies, the explicit incorporation of strategies to support intervention adoption within schools has been suggested to be important [24,30,31]. Such strategies can include teacher professional learning, on-going teacher support, availability of credible leadership and opinion leaders, provision of resources and prompts, and monitoring and feedback of intervention adoption [24,30,31].

Given the lack of multi-component intervention studies that target physical activity levels among adolescents from lower income or disadvantaged groups, the aim of this study is to determine whether a multi-component physical activity intervention implemented in disadvantaged secondary schools can reduce the decline in physical activity associated with adolescence.

## Methods/Design

### Study design

This study will employ a cluster randomised controlled design (Figure 1).

**Figure 1 F1:**
[figure not shown]
CONSORT flowchart describing progress of participants through the study.

The research will be conducted and reported in accordance with the requirements of the Consolidated Standards of Reporting Trials (CONSORT) Statement [32,33]. A randomly selected sample of disadvantaged secondary schools in the study region will be invited to participate. The schools will be randomly allocated to receive a multi-component intervention to be implemented during school terms and to commence after baseline data collection, or to a control group. Data will be collected from students at baseline (when students are in their first year of high school, aged 12–13 years), and from the same cohort of students after 12-months (midpoint) and 24-months post baseline data collection. The primary outcome will be minutes per day and percentage of time in moderate- to vigorous-intensity physical activity (MVPA) at 24-month follow-up.

### Setting

The study will be conducted in the Hunter, Central Coast and Mid North Coast regions of the state of New South Wales, Australia. These regions encompass major city and regional areas (ARIA) [34]. The regions have lower indices of socio-economic status than New South Wales [35] and a population of approximately 64,188 children aged between 12 and 15 years (17.6%) [35].

### Sample/ Participants

#### Secondary schools

Secondary schools in New South Wales cater for students aged from about 12 (Year 7) to 18 (Year 12) years old. Students are required to undertake 300 hours of Health and Physical Education each year, from Year 7 to Year 10 [36,37]. Students also have opportunities to engage in physical activity through school sport (averaging 2 hours per week) [38]. Physical Education is taught by qualified Health and Physical Education teachers.

Of the secondary schools within the study region, those that meet the following criteria will be eligible to participate in the study: Government and Catholic schools; schools with postcodes ranked in the bottom 50% of New South Wales postcodes based on the Socio-Economic Indexes For Australia (SEIFA) [39]; have between 120–200 Year 7 students (to meet sample size requirements); and are not participating in other major physical activity or health intervention studies. Ten schools will be recruited.

#### Students

All Year 7 students in participating schools will be eligible to participate in the study measurement. Classes catering for students with severe physical and mental disabilities will be excluded.

### Recruitment procedures

#### Schools

Prior to recruitment, the study will be promoted to school sector Regional Directors within the NSW Department of Education and Communities (DEC) and the relevant Catholic school Dioceses to gain their support. A random number function in Microsoft Excel will be used to determine the order in which the eligible secondary schools are approached to participate. Invitations to participate will be sent to the 10 randomly selected schools. If a selected school declines, an additional letter will be sent to the next eligible school on the list, until 10 schools accept the invitation to participate.

A letter will be sent to selected schools, detailing the study and inviting participation. Approximately two weeks after the invitation letter is sent to the school, the Principal will be contacted by phone by a member of the research team. A face-to-face meeting will be requested with both the Principal and the Head Health and Physical Education teacher to outline the requirements of the study and request consent.

#### Random allocation of schools

Eligible schools will be classified into two strata based on geographic location (regional or major city) [34]. Research indicates that location may contribute to the varying physical activity levels of adolescents [40]. Four consenting schools will be obtained from the major city strata and six from the regional school strata. Participating schools will be randomly allocated using block randomization (1:1 ratio) to the intervention or control condition using a computerized random number function. Randomization will be undertaken by a statistician not involved in contacting schools or in the study intervention or assessment and will occur after baseline data collection to reduce participation bias from students, teachers and researchers. The school Principal will receive a letter from the study team indicating to which group the school has been allocated. Data collectors will be blinded at baseline and where possible at 12 and 24-months data collection.

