### Statistical analysis – primary outcome

Analyses using cluster-level summaries are more robust than analyses based on individual-level data when there are less than 15 clusters per treatment arm [77]. Therefore the primary outcome for this study will be analysed by calculating the change in the mean number of minutes of moderate to vigorous physical activity within each school and then comparing the school-level means of the intervention group with the school-level means of the control group using a two sample t-test. The main analysis will be conducted with all available data using the intention to treat principle and sensitivity analyses conducted under various assumptions about the missing data mechanism [78]. Per protocol analyses will also be performed where appropriate.

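### The location-stratified allocation of ten schools leaves out the baseline MVPA already collected; using it at allocation and in the analysis would be a cheap, modest improvement

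*Protocol article*

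**What the plan says.** All references are to the protocol article.

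- **Number of schools and strata.** Secondary schools: "Ten schools will be recruited". Random allocation of schools: "Four consenting schools will be obtained from the major city strata and six from the regional school strata". The stated reason for stratifying is that location may be related to adolescents' activity.
- **Method.** "Participating schools will be randomly allocated using block randomization (1:1 ratio) to the intervention or control condition using a computerized random number function", by a statistician who is not involved in contacting schools, intervention or assessment. The text does not say in words that blocks are formed within strata, but that is the natural reading. Block size is not given.
- **Timing.** Randomisation "will occur after baseline data collection to reduce participation bias from students, teachers and researchers". The abstract agrees: "Group allocation and intervention delivery will commence after baseline data collection".
- **Analysis.** Statistical analysis – primary outcome takes the change in mean MVPA within each school and compares the five and five school values by a two-sample t-test. The reason given is: "Analyses using cluster-level summaries are more robust than analyses based on individual-level data when there are less than 15 clusters per treatment arm".

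Baseline MVPA therefore enters the analysis through the change score. No use of it at allocation is described.

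**The concern.** With five schools per arm, randomisation can leave the arms apart at baseline on the outcome itself. Most trials cannot prevent this because the outcome is unknown at allocation. Here all ten schools will have been measured first, and an independent statistician performs the allocation, so the information and the person to use it are both in place.

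The change score removes the baseline difference in full. Only part of a chance difference persists to 24 months, so subtracting all of it over-corrects and adds noise. Adjusting for baseline later repairs this, but costs one of eight degrees of freedom and loses some precision when the arms happen to differ. The allocation cannot be repeated once made. At stake are some precision and the face validity of a ten-cluster result, not the validity of the trial.

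**Working it through.** **Inputs from Sample size:** SD 17.1 min; ICC 0.01; 60 students per school at baseline; 195 per arm at 24 months, i.e. 39 per school; target 5.73 min. **Assumed, not in the document:** correlations between baseline and follow-up (students 0.3–0.7, school effects 0.5–0.8) and any ICC other than 0.01.

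**1. The plan's own figure.** Design effect 1 + (39 − 1) × 0.01 = 1.38; 195/1.38 = 141.3. Detectable difference: 5.71 min by the normal approximation, 5.73 min by the t version with 280 df. The stated 5.73 is reproduced.

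**2. Chance baseline difference.**
- SD of a school mean: 17.1 × √(0.01 + 0.99/60) = 2.78 min.
- SD of the 5 v 5 difference: 2.78 × √(2/5) = 1.76 min, which is 0.10 of the student SD and 31% of 5.73.
- 95% range: ±1.96 × 1.76 = ±3.45 min. Expected absolute difference: 1.40 min.
- Probability of exceeding half the target (2.87 min): 0.10. Probability of exceeding 5.73 min: 0.001.
- At an assumed ICC of 0.05 or 0.10 the SD is 2.77 or 3.67 min, and the probability of exceeding 5.73 is 0.04 or 0.12.

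**3. What the change score leaves.** In the 39 followed-up students the baseline difference has SD 17.1 × √((0.01 + 0.99/39) × 2/5) = 2.03 min. The school-level slope of follow-up on baseline is (0.01 × school correlation + 0.99/39 × student correlation) / (0.01 + 0.99/39). With school correlation 0.8 and student correlation 0.3, 0.5 or 0.7 this is 0.44, 0.58 or 0.73. The over-correction, (1 − slope) × 2.03, has SD 1.14, 0.85 or 0.55 min.

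**4. What balancing can do.** Taking each stratum as one block there are C(4,2) × C(6,3) = 6 × 20 = 120 allocations. Drawing from the best-balanced 30 cuts the SD of the baseline difference in all 60 students per school from 1.76 to 0.38 min. Among the 39 followed up, the fall is only from about 2.0 to 1.1 min.

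**5. How many to keep.** Swapping the arms leaves the absolute difference unchanged, so allocations come in mirror pairs. The smallest two-sided permutation p-value is 2/30 = 0.067 with 30 kept, 2/40 = 0.05 with 40, 2/60 = 0.033 with 60 and 2/120 = 0.017 with all.

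**6. Power at 5.73 min** (simulated; change taken in followed-up students), planned analysis versus constrained allocation plus baseline adjustment:
- ICC 0.01, student/school correlation 0.5/0.8: 0.78 to 0.83.
- ICC 0.05, same correlations: 0.58 to 0.64.
- ICC 0.01, correlations 0.3/0.5: 0.59 to 0.72.

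A repeat with 8,000 trials per scenario and 60 allocations kept agreed within 0.02. In it, adjustment without the constraint supplied most of the gain in the third scenario (0.58 to 0.68, then 0.72 with both). With student correlation 0.7 there was almost no gain (0.91 to 0.92).

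**7. Constraint without adjustment.** The planned t-test becomes conservative, with type I error about 0.03–0.04, and its power hardly moves (0.78 and 0.78 in the first scenario). With adjustment, type I error stays near 0.05.

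**The case against.** The strongest reply is that stratified block randomisation followed by a school-level change analysis is a standard, valid design. Randomisation makes the estimate unbiased, the t-test's error already includes chance imbalance, and the change score subtracts the baseline difference. All of that stands.

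A reader might infer several stronger points that the document does not support:

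- **That schools are allocated without any balancing.** They are not: location is stratified, and the count of 120 allocations depends on it.
- **That the imbalance is large.** On the plan's ICC it is typically 1.4 to 1.8 min and exceeds the target about once in a thousand trials. It becomes large only if the ICC is well above 0.01.
- **That constraining the allocation raises the power of the planned test.** It adds at most about 0.02, because the standard error falls but the test turns conservative.
- **That the change is free.** Some 600 seven-day accelerometer files (10 × 60) would have to be processed and checked for wear time before schools learn their group, which could delay a programme tied to school terms.
- **That the tightest balance is best.** Keeping 30 allocations would stop a two-sided permutation test from reaching 0.05.

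Loss to follow-up also undoes part of the balance. What survives is the smaller point: with both parts adopted, power was never meaningfully worse than planned in the scenarios tried and was often better, without another school or student.

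**Conclusion.** The point holds as an optional improvement to a sound design. The plan accepts a chance baseline difference with SD 1.76 min/day, of which the change score leaves roughly 0.5 to 1.1 min as regression to the mean. Constrained allocation and baseline adjustment together raise power at 5.73 min by roughly 0 to 13 points, with the smallest gain when student MVPA is highly correlated over time. Where the gain is largest, most of it comes from the adjustment.

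The imbalance figure rests on the plan's own SD, ICC and school size. The power figures rest on assumed correlations, on equal school sizes, and on change being taken in followed-up students. Nothing in the document is contradictory or wrong here.

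**What to change.** Adopt both parts or neither.

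**(a) Random allocation of schools.** State that, after baseline, the independent statistician lists the 120 allocations within the two strata and scores each by the between-arm difference in school mean baseline MVPA. The statistician keeps a pre-stated better-balanced set of about 60, in whole mirror pairs, checks that no two schools are always together or always apart, and draws one at random.

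**(b) Statistical analysis – primary outcome.** Adjust the school-level comparison for school baseline mean MVPA. Compute that mean in the students who contribute to the follow-up comparison: in the repeat simulation at student correlation 0.7, with 60 allocations kept, using all 60 baseline students per school instead gave power 0.87 rather than 0.92. A permutation test over the retained set can be named as a check.

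**Cost.** A paragraph in one section, a sentence in the other and a short program; accelerometer files processed before allocation; 7 rather than 8 degrees of freedom. No extra schools, students or staff. If early processing is not feasible, part (b) alone still gives much of the benefit when the correlations are low, and close to none when they are high.

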#### Students

All Year 7 students in the participating schools will be provided an information package that will contain a letter outlining the study and a consent form for parents asking for consent for their child to participate in the study data collection. Parents will be provided with a telephone number where they can leave a message if they do not want to be prompted about consent or do not want their child to participate in the measurement component of the intervention. Two weeks following distribution of the information package, parents who have not returned a consent form or left a message indicating they do not wish to be contacted, will be telephoned by staff employed through the education sector and asked if their child can participate in study measurement. A replacement consent form will be sent to parents providing verbal consent.

A number of strategies that have been used successfully in similar research will be adopted in an to effort maximise parent and student consent. These include having a designated recruitment co-ordinator, promoting the research prior to requests to participate, disseminating materials to maximise parent engagement, and issuing reminders to parents using a variety of methods including phone calls and letters [28,38,41].

### Physical activity intervention

#### Theoretical framework and physical activity content

Consistent with recommendations from reviews to maximise the effectiveness of school-based physical activity studies, the intervention has been guided by social cognitive [42] and social-ecological theories [43] and will be implemented using the World Health Organisation’s (WHO) Health Promoting Schools framework. This framework includes strategies that address the school curriculum, school environment and community [14,29,44-46].

Figure 2 shows the seven physical activity intervention strategies that schools will be facilitated to implement, and the strategies that will be used to increase the extent of intervention adoption. A further description of the physical activity intervention strategies within the Health Promoting Schools framework domains is as follows.

Formal curriculum

1. Implementation of teaching strategies to maximise student activity levels within Physical Education classes. Schools will aim to meet 50% of Physical Education class time in MVPA for their students, a standard recommended by the US Centres for Disease Control (CDC) and Prevention [47]. Health and Physical Education teachers will receive training and resources to assist in maximising moderate- vigorous physical activity, including workshop style sessions that will incorporate a facilitated process for reflection on levels of MVPA in lessons and changing teaching practices to enhance levels of activity. In addition to this training, regular pedometer-based lessons and curriculum material will be introduced to assist teachers [48-50].

2. Development and monitoring of annual individual student physical activity plans in health and physical activity that include: long- and short-term personal goals for improving or maintaining regular physical activity; specific actions and timelines to achieve those goals; fitness assessments; methods to be used to record actions and assess progress; and rewards for achieving goals [51]. Health and Physical Education teachers will be responsible for co-ordinating the development and monitoring of individual physical activity plans. Consistent with the CDC guidelines, students will be encouraged to review their physical activity plans and modify the content regularly [11]. Students will also be given small incentives when their personal goals have been met (such as balls, wrist bands, drink bottles).

3. Implementation of enhanced school sport programs for all students. All students will be scheduled to participate in age appropriate 10-week programs during school sport while they are in Years 7, 8 or 9. The school sports programs will be based on *Program X* and Physical Activity Leaders (*PALs*), both of which have been shown to be efficacious in adolescents [48,52]. These single sex programs include; health-related fitness activities, pedometers for self-monitoring, lunch-time activities, information for parents and interactive seminars [38,48,52]. The programs have been designed to meet the needs of low-active students, and are known to be acceptable and appropriate for such students and improve psychological outcomes [53]. The program content is relevant to all students, and year-wide implementation as a sport option will ensure no student is stigmatised.

School ethos and environment

4. Modification of school policies that encourage low-active students to be more physically active [54]. The policies within each intervention school will be reviewed with the aim of establishing policies that enhance physical activity, and modifying existing policies that may be inhibiting activity. School policies that promote single sex Physical Education classes, modified Physical Education uniforms for girls, mandatory Physical Education and sport, provision of equipment and staff supervision in breaks have been shown to enhance physical activity [55].

5. Implementation of daily physical activity programs for students during school breaks including increasing the availability of facilities and equipment. Intervention schools will be offered equipment and supervised activities in recess and lunch breaks. Supervised activities have been shown to increase the participation of students in recess and lunchtime activities [56]. Through participation in the enhanced sport programs (ie. Program X and PALs), the intervention aims to train students to lead the recess and lunchtime activities over the course of the intervention.

Partnerships and Services

6. Implementation of accessible after-school physical activity programs through linkages with community sporting groups and/or organisations from the fitness industry [54,57]. Links will be established between the school and the broader community to enhance the physical activity opportunities available to students outside of school hours. The types of links established will be based on the criteria used in other physical activity interventions [38,58].

7. Parent engagement: Strategies will encourage parents to; increase their adolescent’s physical activity, be active with their adolescent at home and in the community [59,60]. Regular information will be sent to parents via existing schools newsletters, school website and program newsletters to support the activities occurring within the school. The materials will inform parents of school-based strategies, promote newly established community links and provide ideas to support physical activity outside of school hours. The newsletters will also aim to provide information on physical activity recommendations and strategies to encourage participation, including parent role modelling.

